### 1.3.1 Primary outcome

- Proportion of patients receiving any lumbar imaging (yes/no). Any lumbar imaging will include the following radiology procedures:
  - XR Chest and Spine 2 Regions

## SHaPED trial Statistical Analysis Plan

- XR Chest and Spine 3 Regions
- XR Coccyx
- XR Lumbar Sacrum
- XR Pelvis
- XR Pelvis and Hip Left
- XR Pelvis and Hip Right
- XR Pelvis Hip and Femur Left
- XR Pelvis Hip and Femur Right
- XR Sacroiliac Joints
- XR Sacrum
- XR Skeletal Survey
- XR Spine 4 Region
- XR Spine Lumbar
- XR Spine Lumbosacral
- XR Spine Scoliosis Study
- XR Spine Thoracic Lumbar
- CT Brain and Spine Thoracic and Lumbar
- CT Pelvis
- CT Pelvis and Hip Left
- CT Pelvis and Hip Right
- CT Pelvis and Hips Bilateral
- CT Pelvis and Spine
- CT Sacrum
- CT Spine 2 regions
- CT Spine Lumbar
- CT Spine Lumbar and Pelvis
- CT Spine Cervical Thoracic Lumbar
- CT Spine Thoracic Lumbar
- CT Spine Whole
- MRI Pelvis
- MRI Sacrum
- MRI Spinal Cord Compression
- MRI Spine 2 Regions (User defines)
- MRI Spine Lumbar
- MRI Spine Whole

### **1.3.2 Secondary outcomes**

- Proportion of patients receiving advanced imaging (CT/MRI=yes, X-ray/no imaging=no)

## SHaPED trial Statistical Analysis Plan

- Proportion of patients receiving any strong opioid medication. Any strong opioid will include the following medications:
  - Buprenorphine
  - Fentanyl
  - Hydromorphone
  - Morphine
  - Oxycodone
  - Pethidine
  - Tapentadol
- Proportion of patients receiving any opioid medication. Any opioid will include the following medications:
  - Alfentanil
  - Buprenorphine
  - Codeine phosphate
  - Codeine-aspirin
  - Codeine-ibuprofen
  - Codeine-paracetamol
  - Codeine-paracetamol-doxylamine
  - Dextropropoxyphene
  - Dextropropoxyphene-paracetamol
  - Dihydrocodeine
  - Fentanyl
  - Hydromorphone
  - Morphine
  - Nicomorphine
  - Oxycodone
  - Oxycodone-naloxone
  - Pethidine
  - Remifentanil
  - Sufentanil
  - Tapentadol
  - Tramadol
  - Tramadol-paracetamol
- Proportion of patients receiving other analgesic medications (topical, oral, injection). Other medications were classified according to the Anatomical Therapeutic Chemical (ATC) classification system (table 3). The ATC classification is recommended by the WHO and is widely used internationally in medication use studies:
  - Paracetamol (N02BE01)
  - Non-steroidal anti-inflammatory drugs (M01A, M02AA):
    - Aspirin

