### Secondary objectives

The secondary objectives of the study are:

- To determine if implementation of the ACI model of care significantly reduces the proportion of patients presenting with low back pain who receive opioids in the ED and the proportion of patients admitted to hospital from ED.
- To determine if patient outcomes are not worse with implementation of the ACI model of care in people who present with low back pain in the ED.
- To determine the cost-effectiveness of the ACI model of care compared with usual ED practice for people who present with low back pain.
- To determine the barriers and facilitators to the implementation intervention of the ACI model of care for people who present with low back pain in the ED.

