## **2.8 Analysis of secondary outcomes**

### **2.8.1 Binary outcomes**

All binary secondary outcomes will be analysed using the same strategy as the one applied to the primary outcome, that is using both an unadjusted and adjusted logistic regression model and both by excluding and including the intervention period, thus giving four models. Subgroup analyses will not be conducted on secondary outcomes.

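### The strong-opioid list in SAP 1.3.2 names oxycodone but not oxycodone-naloxone, so a patient whose only listed strong opioid is that combination is coded as having received none

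*Combined protocol and SAP*

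**What the plan says.** SAP 1.3.2 has two opioid outcomes, each defined by a list of drug names.

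- The first is introduced as "Proportion of patients receiving any strong opioid medication. Any strong opioid will include the following medications". It has seven entries: oxycodone, morphine, fentanyl, hydromorphone, buprenorphine, tapentadol and pethidine.
- The second is introduced as "Proportion of patients receiving any opioid medication. Any opioid will include the following medications". It has 22 entries. Oxycodone is one, and "Oxycodone-naloxone" is another, on its own line.

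The SAP does not define what makes an opioid strong, and it does not say whether an entry is matched by product name or by active ingredient. The protocol does not help: its Secondary outcomes section has a single opioid class, set by ATC codes in its Table 3, with no strong category.

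Strong-opioid use is a binary secondary outcome, so SAP 2.8.1 applies: "All binary secondary outcomes will be analysed using the same strategy as the one applied to the primary outcome". That means four logistic models, adjusted and unadjusted, with and without the implementation period. The opioid objective in SAP 1.2 is worded more broadly. It concerns patients "who receive opioids in the ED and the proportion of patients admitted to hospital from ED" and does not mention strong opioids.

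**The concern.** An outcome list works as a coding rule. If the programmer matches on the names as printed, a patient given oxycodone-naloxone and nothing else from the seven is coded yes for any opioid and no for strong opioid. That is hard to defend, because the product contains a drug that the strong list names.

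A second programmer could read oxycodone as an ingredient and code the same patient yes. The two readings give different outcome variables, and the SAP does not choose between them. If the choice is made after results are seen, it becomes a post hoc reclassification of a prespecified outcome.

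**Working it through.** The plan gives no figure to reproduce here, so the check is a comparison of the two lists in SAP 1.3.2, followed by the algebra of the miscoding.

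**1. Compare the lists.** The strong list has 7 entries, and all 7 are in the 22-entry any-opioid list. That leaves 22 − 7 = 15 any-opioid entries that are not counted as strong.

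**2. Search the 15 for a listed strong ingredient.** The codeine entries, the dextropropoxyphene entries, dihydrocodeine, tramadol and "Tramadol-paracetamol", alfentanil, remifentanil, sufentanil and nicomorphine contain none of the seven named drugs. Oxycodone-naloxone does. It is the only such entry.

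**3. Ask whether a parent entry covers its combinations.** Seven of the 22 any-opioid entries are combinations listed by name: four with codeine, and one each with dextropropoxyphene, oxycodone and tramadol. The same habit appears elsewhere in 1.3.2, where ibuprofen and ibuprofen-paracetamol, and orphenadrine and orphenadrine-paracetamol, have separate lines. If a parent entry covered its combinations, these lines would be redundant. The more literal reading is therefore that names are products, and that oxycodone on the strong list does not reach oxycodone-naloxone.

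**4. Who is miscoded.** Only patients given oxycodone-naloxone and none of the seven listed drugs. A patient also given morphine, for example, is still coded yes.

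**5. What this does to the comparison.** Let *p* be the proportion who received one of the seven drugs or oxycodone-naloxone. Let *s* be the share of those patients whose only such drug was oxycodone-naloxone. The literal rule records *p*(1 − *s*). With subscript 1 for intervention and 0 for control, the recorded difference is

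*p*₁(1 − *s*₁) − *p*₀(1 − *s*₀).

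- If *s*₁ = *s*₀ = *s*, this equals (*p*₁ − *p*₀)(1 − *s*). The outcome is under-counted in both conditions and a real difference shrinks by the factor 1 − *s*. The odds ratio also moves towards 1. No effect is created where none exists.
- If *p*₁ = *p*₀ = *p* but *s* changes, this equals −*p*(*s*₁ − *s*₀). A rise in *s* after crossover appears as a fall in strong-opioid use that did not happen, and the reverse for a fall in *s*.

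The model in SAP 2.6.1 has a cluster effect and a period effect. These largely absorb stable differences in product mix between EDs and drift common to all EDs. A change in *s* that follows each ED's own crossover would load on the intervention term.

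**6. Size.** The calculation needs *s*₀ and *s*₁. Neither document gives a count for oxycodone-naloxone, so no figure can be put in.

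**The case against.** The strongest reply is that this is an ambiguity of wording, not a certain error. The strong list says what the outcome will include and does not say that nothing else counts. SAP 2.6.2 records that opioid data were extracted by hand for some EDs without an electronic medication system, and the SAP does not describe how combinations were coded. That oxycodone-naloxone sits in the data as its own item is inferred from the lists. All of this stands. It does not remove the point, because the SAP's own habit of listing combinations separately makes the product reading the more literal one, and no text overrides it. A deliberate exclusion is also possible, but no reason is given.

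It is also fair to say that the intervention gives no stated reason for the product mix to change. The education and feedback in protocol Appendix 3 address imaging, opioids and admissions as a whole, and nothing there favours or discourages oxycodone-naloxone relative to oxycodone. That stands too, and it is why a material bias is possible but not shown.

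Four stronger readings are tempting and are not supported.

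- A reader might infer that every patient given the combination is lost from the outcome. Step 4 shows that only those with no other listed strong opioid are.
- A reader might infer that the trial's opioid objective is compromised. The objective in SAP 1.2 concerns opioids in general and is served by the any-opioid outcome, which names oxycodone-naloxone.
- A reader might put a size on the error by multiplying the 62% opioid use in the protocol's Introduction by a guessed product share. The 62% is background from a cited study whose title refers to United States emergency departments, not a planning value for these four EDs, and the documents give no basis for any share.
- A reader might extend the point to alfentanil, remifentanil, sufentanil and nicomorphine. None contains a drug named on the strong list, and since strong is not defined, their status cannot be settled from the documents.

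**Conclusion.** The concern holds, within narrow limits. Read literally, the strong-opioid definition in SAP 1.3.2 misclassifies patients whose only listed strong opioid is oxycodone-naloxone, and nothing else in the protocol or SAP corrects it. This rests on entries being matched as product names, which is the more literal reading but is not stated.

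One secondary outcome is affected, in its four models. The primary imaging outcome and the any-opioid outcome are not. The number of patients cannot be computed from the documents and is probably small. With a stable product mix the consequence is a slight under-count and slight attenuation; a material bias in the treatment effect would need the mix to change at crossover. The case for acting is that the rule is wrong on its face and trivial to correct, not that a large error has been shown.

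**What to change.** Before analysis, do one of the following in SAP 1.3.2:

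- add oxycodone-naloxone to the strong-opioid list; or
- state that entries on the strong list are matched by active ingredient, so that oxycodone covers oxycodone-naloxone.

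Apply the chosen rule in the same way to electronic and hand-extracted records. If the combination was left out on purpose, say so and give the reason.

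The cost is one line in the SAP and one line of code. The product name is already in the any-opioid list, so no new data item has to be defined. The change concerns outcome coding only and has no bearing on clinical management.

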## SHaPED trial Statistical Analysis Plan

- Celecoxib
- Diclofenac
- Diclofenac topical
- Etoricoxib
- Ibuprofen
- Ibuprofen topical
- Ibuprofen-paracetamol
- Indomethacin
- Ketoprofen
- Ketorolac
- Mefenamic acid
- Naproxen
- Parecoxib
- Piroxicam
- Piroxicam topical
- Sulindac
- Muscle relaxants (M03):
  - Baclofen
  - Dantrolene
  - Orphenadrine
  - Orphenadrine-paracetamol
  - Vecuronium
- Corticosteroids (H02):
  - Cortisone
  - Dexamethasone
  - Hydrocortisone
  - Methylprednisolone
  - Prednisolone
  - Prednisone
  - Triamcinolone
- Benzodiazepine derivatives (N05BA):
  - Alprazolam
  - Bromazepam
  - Clobazam
  - Clonazepam
  - Diazepam
  - Flunitrazepam
  - Lorazepam
  - Midazolam
  - Nitrazepam
  - Oxazepam
  - Temazepam
  - Zolpidem

## SHaPED trial Statistical Analysis Plan

- Zopiclone
  - Antiepileptics (N03A):
    - Carbamazepine
    - Ethosuximide
    - Gabapentin
    - Lacosamide
    - Lamotrigine
    - Levetiracetam
    - Oxcarbazepine
    - Phenobarbital
    - Phenytoin
    - Pregabalin
    - Sodium valproate or valproic acid
    - Tiagabine
    - Topiramate
    - Vigabatrin
    - Zonisamide
  - Antidepressants (N06A):
    - Amitriptyline
    - Bupropion
    - Clomipramine
    - Dosulepin
    - Doxepin
    - Duloxetine
    - Duloxetine
    - Fluoxetine
    - Imipramine
    - Mianserin
    - Mirtazapine
    - Moclobemide
    - Nortriptyline
    - Paroxetine
    - Reboxetine
    - Sertraline
    - Venlafaxine
    - Vortioxetine
- Proportion of patients admitted from ED to:
  - Hospital ward
  - Emergency Medical Unit (EMU) or Short Stay Unit (EDSSU)
- Time in ED (triage time to discharge or admission time)
- Proportion of patients referred for a consultation in the ED:
  - Pain management

- Rheumatology
  - Surgery
- Proportion of patients representing to the same ED within 48 hours
- Total health system costs (including intervention costs and health service delivery costs)
- Pain intensity (Numeric Rating Scale, range 0–10)
- Physical function (PROMIS Short Form—Physical Function 4a)
- Quality of life (PROMIS Scale—Global Health item 1)
- Satisfaction (EDPEC survey item 31)

### **1.3.3 Sample size**

Based on the effect size of 10% absolute reduction (from 30% to 20%) in lumbar imaging referrals (primary outcome), combined with an alpha of 0.05 and assuming an intraclass correlation coefficient of 0.1, a total number of 1,920 low back pain presentations (on average 480 per cluster) to EDs is needed for this stepped-wedge cluster trial with 80% power. For patient-reported outcomes, we have run a power calculation for pain intensity (range 0–10). We have assumed a non-inferiority margin of 1-point (i.e. we accept a mean difference in pain scores of up to 1 unit). We also assumed a standard deviation of 2.5 and an ICC of 0.05 based on previous low back pain trials. The sample size required for 80% power is 30 subjects per ED, per period/month. Given that the 'core trial' contains five periods, this means a total of 150 subjects per ED or 600 overall.

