## Secondary objectives

The secondary aims of the study are:

- To determine if implementation of the ACI model of care significantly reduces the proportion of patients presenting with low back pain who receive opioids in the emergency department and the proportion of patients subsequently admitted to hospital.
- To determine if implementation of the ACI model of care significantly improves patient outcomes in people who present with low back pain in the emergency department.
- To determine the cost-effectiveness of the ACI model of care compared with current emergency department practice for people who present with low back pain.
- To determine the barriers and facilitators to the implementation intervention of the ACI model of care for people who present with low back pain in the emergency department.

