| Lumbar radiculopathy (disorder)                                               | 128196005 |
| Sciatica (disorder)                                                           | 23056005  |
| Spinal stenosis of lumbar region (disorder)                                   | 18347007  |

Patient-reported outcomes were collected using automated text messaging at one week (primary time point) and again at two and four weeks after index ED presentation. Between July 2018 and December 2018, all eligible patients presenting to the participating EDs were invited to complete a brief self-reported online survey at ED discharge. Reminder messages were sent to non-responders, and those who did not respond to the reminder message were contacted via telephone. We invited a total of 807 eligible patients and 416 (52%) agreed to participate and completed week-1 survey. Of those, 360 (87%) completed week-2 and 351 (84%) week-4 surveys.

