### **2.8.3 Patient reported outcomes**

All patient reported outcomes will be treated as continuous outcomes and therefore analysed following the strategy described in Section 2.8.2.

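### The 80% power for pain non-inferiority holds only if the implementation cells are analysed and 600 patients respond; neither is so in the main analysis, and no rule ties the not-worse objective to the 1-point margin

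*Combined protocol and SAP*

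**What the plan says.** SAP 1.2 sets this secondary objective: "To determine if patient outcomes are not worse with implementation of the ACI model of care". The protocol's objective was one of superiority, asking whether implementation "significantly improves patient outcomes in people who present with low back pain in the emergency department".

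SAP 1.3.3 gives the power calculation for pain on the 0–10 scale. On the margin: "We have assumed a non-inferiority margin of 1-point (i.e. we accept a mean difference in pain scores of up to 1 unit". On variability: "We also assumed a standard deviation of 2.5 and an ICC of 0.05 based on previous low back pain trials". On size: "The sample size required for 80% power is 30 subjects per ED, per period/month", and then "Given that the 'core trial' contains five periods, this means a total of 150 subjects per ED or 600 overall". It does not give a significance level for this calculation. Section 2.1 makes every test two-sided at 5%.

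SAP 1.3 reports the survey, run from July to December 2018: "We invited a total of 807 eligible patients and 416 (52%) agreed to participate and completed week-1 survey". Section 2.6.2 rules out imputation of patient-reported outcomes, so the week-1 analysis cannot use more than 416 patients.

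On analysis, 2.8.3 says: "All patient reported outcomes will be treated as continuous outcomes and therefore analysed following the strategy described in Section 2.8.2". Section 2.8.2 replaces the logistic model with a linear one, reports a mean difference with a 95% CI, and otherwise follows the binary outcomes. Section 2.8.1 fits those with and without covariates, and with the implementation period both excluded and included. Table 3 in 2.2 marks the implementation cells as not analysed, and 2.7.2 calls the including analysis exploratory.

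**The concern.** The power statement and the analysis describe different data sets. The power statement counts every ED in every core period. The main analysis removes one period per ED, the one in which that ED is being switched over. In a stepped wedge, cells next to the crossover carry much of the information on the effect, so the loss of power is larger than the loss of patients. The number of responders also fell well short of 600.

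The 1-point margin appears only in the sample-size section. The analysis sections contain no non-inferiority hypothesis and no rule comparing the confidence interval with the margin. They do not say which of the four models decides, and they give no margin for function, quality of life or satisfaction.

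The trial aims to reduce imaging, opioid use and admission. The patient-reported outcomes are where a reader will look for assurance that patients did not fare worse. With imprecise data and no decision rule, a non-significant two-sided result could be taken as that assurance.

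**Working it through.** **Inputs (SAP 1.3.3 unless noted).** Margin 1; SD 2.5; ICC 0.05; four EDs, one crossing per step; 30 per cell over five periods; two-sided 5% (2.1), i.e. the upper 95% confidence limit against the margin; 416 week-1 responders (1.3).

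**Method.** Linear model with fixed period effects and a random ED effect. For each ED, V = τ²J + (σ²/m)I, with m patients per cell. Var(effect) is the effect element of (ΣX′V⁻¹X)⁻¹, and excluded cells are deleted rows. With a true difference of zero, power = Φ(1/SE − 1.96).

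The SD can be read in two ways, and the ranges below cover both:
- Total SD: σ² = 6.25 × 0.95 = 5.9375; τ² = 6.25 × 0.05 = 0.3125.
- Within-ED SD: σ² = 6.25; τ² = 6.25 × 0.05/0.95 = 0.329.

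**Step 1: reproduce the stated figure.** With no cells missing there is a closed form:

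Var = I·s(s + Tτ²) / [(IU − W)s + (U² + ITU − TW − IV)τ²], where s = σ²/m.

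Here I = 4 EDs, T = 5 periods, U = 10 intervention cells, W = 30 (squared column totals summed) and V = 30 (squared row totals summed; a count here, not the matrix above). On the total-SD reading:
- s = 5.9375/30 = 0.1979
- numerator = 4 × 0.1979 × (0.1979 + 1.5625) = 1.394
- denominator = 10 × 0.1979 + 30 × 0.3125 = 11.354
- Var = 0.1227, SE = 0.350, power = Φ(2.854 − 1.96) = 81.4%

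The within-ED reading gives SE 0.359 and 79.4%. The stated 80% reproduces with all 20 cells analysed. One-sided 5% would give 87–89%, so two-sided 5% is the level that matches.

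**Step 2: drop the implementation cells, keeping 30 per cell.** This leaves 16 of 20 cells and 480 of 600 patients. SE is 0.492–0.505 and power 51–53%.

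**Step 3: use the 416 responders.** Counts by ED and period are not given, so an even spread is assumed. The survey window covers periods 13–18 of Table 3 plus late December; the power calculation used five periods. Both are shown.

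| Model and spread of the 416 | Per cell | SE | 95% CI half-width | Power |
|---|---|---|---|---|
| Excluding; six periods, spread over all 24 cells (347 analysed) | 17.3 | 0.601–0.617 | 1.18–1.21 | 37–38% |
| Excluding; five periods, spread over all 20 cells (333 analysed) | 20.8 | 0.580–0.595 | 1.14–1.17 | 39–41% |
| Excluding; six periods, all 416 in analysed cells | 20.8 | 0.553–0.567 | 1.08–1.11 | 42–44% |
| Excluding; five periods, all 416 in analysed cells | 26.0 | 0.525–0.539 | 1.03–1.06 | 46–48% |
| Including; six periods | 17.3 | 0.437–0.448 | 0.86–0.88 | 61–63% |
| Including; five periods | 20.8 | 0.415–0.426 | 0.81–0.84 | 65–67% |

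In every excluding row the half-width is above 1, so an observed difference of zero would not meet the margin. In the including rows it would.

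**Step 4: risk of misreading.** If pain were truly 1 point worse, the two-sided test would be non-significant with probability of about 1 − power: 52–63% in the excluding model and 33–39% in the including model.

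**Step 5: sensitivity.** From the six-period rows on the total-SD reading, illustrative uneven ED sizes give 32–41% (excluding) and 58–64% (including). ICC from 0.01 to 0.10, with within-ED correlation across periods either constant or reduced to 0.8 of its value, gives 30–43% and 51–67%. On the total-SD reading, 80% power with implementation cells excluded needs about 61 per cell over five periods (61 × 16 = 976 analysed) or 53 over six (53 × 20 = 1,060). Both exceed the 807 patients invited.

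**The case against.** **The planning sum is correct.** This stands. 30 × 5 × 4 = 600, and 80% reproduces for the design as drawn. A shortfall in responders does not make a planning calculation wrong. The point is a mismatch between that design and the main analysis, not an arithmetic slip.

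**The plan also fits a model including implementation.** This stands too. In that model power is 61–67% and an observed zero would meet the margin. A reader might infer from the excluding model alone that the data could never meet the margin; the documents do not support that. But 2.7.2 labels the including analysis exploratory, and it does not reach 80% either.

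**A single figure such as 38% is too firm.** Agreed. It needs six periods and an even spread over all 24 cells, and the SAP gives no counts to confirm that. Only a range can be defended.

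**The pieces of a non-inferiority reading are there.** Partly right. The margin is stated for pain and a 95% CI is promised, so an analyst could put them together. A reader might infer that the SAP intends to take a non-significant difference as proof of no harm, but no section says so. What is missing is the sentence joining the interval to the margin.

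**Power restated after recruitment adds little, because the interval shows the precision.** Fair once results exist. But 1.3.3 states 80% in a document that already reports 416 responders, and the text should not leave that figure unqualified.

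**The changed objective proves nothing improper.** Agreed. The SAP reports response counts, not outcomes by group. It does not show that the move from superiority to not worse was driven by data.

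**Conclusion.** The concern holds as a mismatch between the sample-size design and the analysis, together with a missing decision rule. The stated 80% applies to 600 patients with every core cell analysed. Excluding the implementation cells brings it to 51–53% with 600. With 416 responders it is about 37–48% in the excluding model (CI half-width 1.03–1.21) and about 61–67% in the including model (0.81–0.88).

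The figures for 416 rest on the SAP's SD, ICC and margin, two-sided 5%, and responders spread evenly over five or six periods. The normal approximation with four EDs is generous, and a small-sample correction would lower them. At two-sided 5%, no variant run with 416 responders reaches 80%.

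These are secondary outcomes and the primary analysis is not affected. The change should be made, but the trial's main conclusion does not depend on it.

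**What to change.** 1. In SAP 1.3.3, state that 80% applies only to 600 patients with all cells analysed. Add the ranges for 416 responders, 37–48% excluding and 61–67% including the implementation period, with the assumptions behind them. Responder counts by ED and period, if available, would allow one figure per model.
2. In SAP 2.8.3, state that week-1 pain is not worse only if the upper limit of the two-sided 95% CI for intervention minus control, from the model excluding the implementation period, is below 1 point. Otherwise the result is inconclusive, and a non-significant difference does not support the claim.
3. Report function, quality of life and satisfaction as estimates with CIs and no not-worse claim, since they have no margin.
4. In SAP 1.2, note that this objective differs from the protocol's superiority objective.

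The cost is a few sentences in the SAP. No new data or models are needed. The downside is a less favourable power figure and a claim that is harder to make.
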